## Abstract

**Objective:**

Autism spectrum disorder (ASD) is a neurodevelopmental condition with limited effective treatment options, including Applied Behavior Analysis, Transcranial Magnetic Stimulation, and certain medications aimed at managing associated behavioral and emotional regulation challenges. Primary interventions include educational training and behavioral modifications. However, long-term, intensive, and individualized rehabilitation training strategies are lacking, and new rehabilitation tools therefore urgently need to be developed. Virtual reality (VR) is a promising digital rehabilitation tool that may support the development of essential life skills, such as social communication and daily living abilities, in many children and adolescents with ASD. Herein, we introduce a protocol for an initial multicenter randomized controlled trial focused on preschool-aged children with ASD. This trial aims to investigate the clinical efficacy of behavioral training for young children with ASD utilizing VR technology.

**Methods:**

A total of 160 children aged 4–7 years with high-functioning ASD will be assigned to either the trial or control group in a 1:1 ratio. The trial group will undergo behavioral training based on VR technology and early family intervention guided by the rehabilitation team, whereas the control group will undergo early family intervention guided by the rehabilitation team. Both arms will undergo twice weekly sessions of either the trial or control intervention modality performed over 12 consecutive weeks. Outcome assessments will be performed at the start of the trial, throughout the intervention phase, and at follow-up intervals during the study.

**Discussion:**

The primary aim of this trial is to determine the clinical effectiveness of cognitive training using VR technology in children with ASD.

**Clinical trial registration:**

Chinese Clinical Trial Registry identifier, ChiCTR2400094189.

## Introduction

1

Autism spectrum disorder (ASD) is a complicated neurodevelopmental condition characterized by several core symptoms, including social difficulties, restricted interests, and repetitive, stereotyped behaviors (1). The prevalence of ASD is on the rise, with roughly 1 in 36 8-year-old children in the United States currently meeting the diagnostic criteria for ASD (2). Conversely, the prevalence of ASD among children aged 6–12 years in China is around 0.7% (3). Children with ASD generally face a challenging prognosis, with a restricted ability to live, learn, and work independently as adults. Individuals diagnosed with ASD commonly encounter significant challenges in achieving independence in adulthood, impacting their capacity to live, learn, and work independently. Zhao et al. previously conducted research examining the economic impact of ASD in China. In this study, the overall annual cost of ASD in 2020 was calculated as $6,706.44 per person. Further, by calculating the prevalence of ASD among the population of China, it was estimated that approximately 6,233,127 individuals have ASD in the country. Based on these values, an estimated economic burden of $41.8 billion per year was calculated, indicating that ASD represents an important public health issue (4).

ASD is a lifelong condition with limited effective treatment options, for which the main interventions are currently based on education and behavior modification (5). However, most therapeutic institutions (e.g., speech therapy, psychotherapy, game therapy) require high-quality professionals and therapeutic scenarios, and they are often concentrated in large cities, where treatment is costly (6). Overall, treatment costs at city-based facilities are prohibitively high, posing a significant barrier to timely treatment access among children from low-income families (7).

Recent research has presented substantial evidence highlighting the wide therapeutic potential of digital health interventions (DHIs), including computer-assisted therapy, wearable technology, and smartphone applications (8). Compared to traditional intervention models that require offline one-on-one sessions with an expert, the use of DHI technology can scale up services at a relatively low cost, thereby overcoming many of the problems of traditional therapies, including high cost, difficulty to access, inefficiency, and lack motivation (9). Virtual reality (VR) technology, as a type of DHI, utilizes advanced computer technology to develop immersive virtual environments that integrate realistic visual, auditory, and haptic sensations where users can interact with objects in a virtual world in a natural manner using assistive devices. Further, they can interact with each other, thereby creating the feeling and experience of existing in the real environment (10). Previous studies have developed many VR systems for application to improve social skills (11), life skills (12), and social adaptability (13) in children with ASD. The findings from these studies have shown that children can understand, interact with, and respond appropriately to virtual environments, with the potential for these skills to generalize to real-life situations (14).

In comparison to traditional intervention models, VR technology has many advantages, including that it offers absolute control over input stimuli and environmental factors, provides a safe place for learning rules and repetitive training, and further reduces the need for real-world social interactions. These benefits can help alleviate sources of anxiety in children with ASD, thereby addressing their psychological needs (15). Children with ASD often show superior visual information input and processing skills, while their thinking can be characterized by visualization and concreteness (16). VR technology provides an optimal method of presenting information to attract the attention and interest of children with ASD. Further, VR learning scenarios can be designed to replicate various real-world situations, thereby allowing students to rehearse and implement their skills in a focused setting (17). This technique thus represents an effective method of presenting information to attract and maintain the interest of children with ASD. Finally, VR technology can facilitate the simultaneous training of multiple patients for interventions, while its integration with the internet can enable the performance of teletherapy, thus reducing the number of offline interventions and medical costs for families of children with ASD (18).

Early intervention training has been demonstrated to notably enhance developmental, behavioral, and core symptoms among children with ASD, resulting in positive physical, social, and emotional developmental outcomes, in addition to increased verbal and nonverbal communication abilities, which is crucial in influencing the prognosis of children with ASD (19). Nevertheless, the majority of previous intervention training protocols utilizing VR technology in children with ASD have concentrated on patients aged from 5-15.5 years. Overall, the majority of studies have concentrated on school-age and adolescent populations, with fewer studies investigating the impact of such interventions on preschool-age children (14).

The current state of VR technology presents several challenges. First, the majority of current VR systems employ head-mounted displays (HMDs), which rely on spectacle-like displays that obscure the user’s vision to present a three-dimensional view of the scene. However, this approach can result in adverse effects in some participants, such as cybersickness, a physical condition marked by symptoms like eyestrain, headache, dizziness, and nausea (20). In some cases, the use of these devices can also lead to anxiety and mood swings in children (21). Consequently, it is generally advised that head-mounted devices not be utilized by individuals under the age of 7, as the visual centres of these targeted individuals have not yet developed to the point where they are capable of effectively utilizing such devices (22). Additionally, younger children are more susceptible to training unsustainability, due to the size and weight of the devices, which can cause mobility problems and lead to physical discomfort. Finally, the inability of younger children to comprehend the precise operation and regulations of complex wearable VR technology can impede their ability to utilize these systems effectively, which can subsequently affect the efficacy of training (23).

To overcome these shortcomings of wearable technologies in the field of VR, we designed a behavioral training system based on VR technology to establish a digital intervention training platform. This system comprises three components: a nonwearable VR interactive game, a real-time detection system, and a cloud platform for assessment and management. This system was designed with the aim of enhancing cognitive functioning among children with ASD.

The diagnosis of ASD relies predominantly on behavioral observations and scale assessments, which are both time-consuming and inefficient. Furthermore, this process is susceptible to various external factors, including the psychological state of patients with ASD, cultural background of caregivers, experience of evaluators, and other variables. Consequently, these methods are prone to subjectivity and bias, which can result in a high rate of missed diagnoses. Therefore, the current protocol was designed to utilize both traditional psychometric scales and functional near-infrared spectroscopy (fNIRS) to evaluate changes in cerebral function in preschool-aged children with ASD prior to and following intervention. The fNIRS method employs near-infrared light (650–950 nm), which penetrates biological tissues to non-invasively monitor cortical activity. fNIRS is a non-invasive method for imaging the brain that monitors cerebral cortical activation by measuring the levels of two hemodynamic parameters: oxygenated haemoglobin (oxy-Hb) and deoxyhaemoglobin (de-Hb). These parameters allow the generation of a comprehensive picture of brain function (24).

This protocol describes an upcoming randomized, controlled, parallel-group, non-inferiority trial utilizing digital technology to implement a behavioral training system based on VR technology in preschool-aged children with ASD. The protocol includes subgroup randomization in conjunction with a 1:1 allocation, to ensure the random allocation of 160 participants to the two groups. The intervention group will receive cognitive behavioral training based on VR technology, in addition to early family intervention under the guidance of the rehabilitation team. Conversely, the control group will receive only early family intervention under the guidance of the rehabilitation team. The effectiveness of cognitive-behavioral training utilizing VR technology in children diagnosed with ASD will be explored by analysing the effects of different modes of rehabilitation training. Additionally, resting-state fNIRS will be used to objectively assess pre- and post-intervention functional brain changes.

We hypothesized that the intervention group would exhibit a potentially positive impact on ASD-related core symptoms, in terms of scale scores and brain function data compared to the control group.

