### Randomization and blinding

2.5

Participants will be assigned randomly to either the experimental or control group in a 1:1 ratio, with randomization lists constructed by an independent statistician using SAS version 9.4 software. Group assignments were concealed using sequentially numbered, opaque, sealed envelopes prepared in advance. Upon enrollment, research staff opened the next envelope in the sequence to reveal the participant’s group assignment. Due to the nature of the intervention, blinding participants or therapists to group allocation was not feasible. However, to reduce assessment bias, all outcome evaluations will be conducted by independent assessors who are blinded to group assignments. To further ensure the reliability of outcome measurements, inter-rater reliability will be evaluated using intraclass correlation coefficients for clinician-administered observational tools such as the ADOS-2 and CARS. The results of the trial, including the patient’s identifying information and details of the intervention, will be de-identified. Final analyses will be performed by a statistician who remains blinded to group allocation.

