### Settings

2.9

The VR-technology-based intervention in the trial group will be implemented offline at each hospital, whereas the control group will undergo early home intervention after the parents are trained. Both groups will be required to undergo early home interventions guided by a rehabilitation team. A gradual approach to early family interventions will be provided by therapists (licensed psychologists and speech therapists) trained in performing early family interventions. These therapists will introduce concepts and strategies, demonstrate their use, and guide the parents in practicing them. The instructions provided by the therapist to each parent-child dyad will remain consistent throughout the study.

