Data analyses will be performed using SPSS software (version 26; IBM Corp.). Paired-sample t-tests will be employed to assess for pre- and post-treatment comparisons between normally distributed measures. Similarly, the Kappa consistency test will be used to perform pre- and post-comparisons of count data. Independent sample t-tests will be employed for between-group comparisons of normally distributed measures, while nonparametric tests will be utilized for between- and within-group comparisons of non-normally distributed measures. Repeated ANOVAs will be conducted to evaluate the treatment effects within each group. The goal of this study is to identify any differences in variables between baseline and post-test measurements in both the treatment and control groups. The factors considered include time (before and after) and group (experimental vs. control), with each measure serving as a dependent variable. For measures that meet the normality test, means ± standard deviation will be used to describe results. Conversely, medians and percentiles will be employed for measures that do not meet the normality test. Count data will be presented as the median and interquartile range. Statistical significance will be defined as a p-value of 0.05 or less. To manage missing outcome data, we will assume that data are missing at random and will apply multiple imputation as the primary approach. Bonferroni correction adjustments will be applied where appropriate to control for the risk of Type I error due to multiple comparisons.

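### The Introduction announces subgroup randomisation, but neither the allocation procedure nor the between-group analysis carries it through; if the subgroups are prognostic strata, the planned test is conservative

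*Protocol article*

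**What the plan says.** The Introduction of the protocol article describes the allocation in one sentence: "The protocol includes subgroup randomization in conjunction with a 1:1 allocation, to ensure the random allocation of 160 participants to the two groups". It does not define the term and names no factor that would form the subgroups.

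Section 2.5 (Randomization and blinding) gives the procedure. Children are allocated "in a 1:1 ratio, with randomization lists constructed by an independent statistician using SAS version 9.4 software". The assignments sit in sequentially numbered sealed envelopes, and at enrolment "research staff opened the next envelope in the sequence". No subgroup, stratum, centre or block is mentioned.

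The Abstract calls the study "an initial multicenter randomized controlled trial", and section 2.9 (Settings) says that the VR training is "implemented offline at each hospital". Hospital is therefore an obvious candidate stratum, but no section says that it is one.

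Section 3 (Statistical analysis) plans independent-sample t-tests between the arms, or nonparametric tests when a measure is not normal, and repeated ANOVAs. It describes the model as follows: "The factors considered include time (before and after) and group (experimental vs. control"). No randomisation subgroup or hospital term appears.

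**The concern.** The article announces a restricted allocation in one place, and neither its own procedure nor its own analysis takes it up.

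This matters because the right standard error depends on how children were allocated. When arms are balanced within strata, differences between strata cannot contribute to the difference between arms. An unadjusted t-test still counts those differences as noise. The interval is then wider than it needs to be, the test rejects less often than its nominal 5%, and power is lost. Interval width carries extra weight because the Introduction and section 2.1 label the trial non-inferiority, where the conclusion rests on a confidence limit.

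Hospital could plausibly matter for ADOS-2. Training is delivered at each site, section 2.8.1 keeps the same therapist with a child, section 2.7 keeps the same clinician for a child's pre- and post-intervention assessments, and the Introduction itself lists evaluator experience among the influences on scale assessment.

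**Working it through.** **Inputs from section 2.2.** SD 4.1, difference 2 points, α = 0.05, power 0.80, 72 children (read as per group, because 72/0.9 = 80 per group), 10% loss, 160 in total. The article does not say whether α is one- or two-sided; two-sided is assumed here.

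**Input not in the documents.** R2, the share of outcome variance explained by the randomisation subgroups. It is assumed to lie between 0 and 0.30.

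**The plan's own figure.** The two-sided normal formula gives n = 2 × (1.96 + 0.842)² × 4.1² / 2² = 66 per group, and the t-test gives 67. The stated 72 is not reproduced, but the gap is in the direction of more children and is a separate matter. The step from 72 to 80 does reproduce. The figure of 72 per arm is used below.

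**Standard errors.**
- Reported by the unadjusted test: SE = 4.1 × sqrt(2/72) = 0.683. The 95% half-width is 1.96 × 0.683 = 1.34 points, whatever R2 is.
- True SE under allocation balanced within strata: 0.683 × sqrt(1 − R2).
- Ratio of reported to true SE: 1/sqrt(1 − R2).

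**Consequences.**
- True two-sided error of the unadjusted test: 2 × [1 − Φ(1.96/sqrt(1 − R2))].
- Power for 2 points, unadjusted: Φ((2 − 1.34)/true SE).
- Power for 2 points, with strata in the model: Φ(2/true SE − 1.96).

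| Assumed R2 | SE ratio | True error, unadjusted | Half-width unadjusted / with strata | Power unadjusted / with strata |
|---|---|---|---|---|
| 0 | 1.00 | 5.0% | 1.34 / 1.34 | 83% / 83% |
| 0.10 | 1.05 | 3.9% | 1.34 / 1.27 | 85% / 87% |
| 0.20 | 1.12 | 2.8% | 1.34 / 1.20 | 86% / 91% |
| 0.30 | 1.20 | 1.9% | 1.34 / 1.12 | 88% / 94% |

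A simulation with four equal strata of 36 children, exact balance within each and 20,000 runs per row gave errors of 4.9%, 4.0%, 3.0% and 2.1%, in line with the formula.

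**Other readings of the allocation.** If subgroup means blocks that do not follow a prognostic factor, R2 is about 0 and the first row applies. If allocation is simple, the unadjusted standard error matches it.

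**Limit of the table.** It applies to the between-group t-test. For a comparison of change from baseline, the relevant R2 is the strata's share of the variance in change, because stable differences between strata cancel.

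**The case against.** The strongest reply is that no contradiction is proved. Section 2.5 refers to lists in the plural, and opening the next envelope in a sequence fits one sequence per site or stratum as well as a single one. The section is silent on strata; it does not rule them out. The term in the Introduction may be a loose rendering of block randomisation, since the purpose given there is allocation to two groups and no prognostic factor is named. Section 3 says that the factors include time and group, which is not strictly an exhaustive list. An article may also leave strata and block sizes to a fuller document. Finally, any error is on the safe side, and unadjusted power exceeds the planned 80% in every row of the table.

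Most of this stands, and it excludes several stronger readings that a reader might infer:

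- *That allocation certainly runs through one sequence without subgroups, so that the two sections cannot both be true.* The text does not say so.
- *That the planned error bars are wrong outright.* That requires real strata, strata that are prognostic, and a final model that omits them. The article establishes neither of the first two.
- *That the trial risks excess false positives.* The error falls below 5%; it does not rise.
- *That hospitals are liable to badly uneven arms, so that hospital-specific blocked lists should be introduced now.* Hospital sizes and unrestricted allocation would both have to be assumed. Chance imbalance does not invalidate the test under simple randomisation. With unblinded therapists, small site blocks also make the next assignment easier to guess.

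One part of the reply does not hold. The point is not that a detail was left out. The article chose to name an allocation method and to state the between-group tests, and the two have not been connected.

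**Conclusion.** The point holds as an unresolved inconsistency with a conditional, conservative consequence. The Introduction names a form of allocation that section 2.5 does not describe and section 3 does not use.

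If the subgroups are prognostic strata, ignoring them inflates the standard error by 0 to about 20%, lowers the true two-sided error from 5.0% to about 2%, and gives up between 0 and about 6 percentage points of power (at R2 = 0.30, 93.8% − 87.6% = 6.2). These sizes rest on the assumed R2 of 0 to 0.30, 72 evaluable children per arm, SD 4.1 and balance within strata. If the subgroups are blocks only, nothing beyond the wording is affected.

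The change is worth making because it is nearly free and the trial is still recruiting, not because the planned test would mislead.

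**What to change.** 1. Make the Introduction and section 2.5 give the same account of what is actually done: simple, blocked or stratified allocation and, if stratified, by which factors. If no subgroups are used, delete the phrase from the Introduction.
2. In section 3, specify that the between-group comparison of ADOS-2 and the other scales comes from a model with arm, the actual randomisation strata and hospital as factors. Where hospital was not a stratum, including it is for precision in a multicentre trial and not to rescue validity.
3. Settle this before outcome data by arm are examined.

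The cost is wording in three places and a few degrees of freedom (with four strata, 3 of the 142 left after two arm means from 144 children). It needs no extra children or visits, and no change to how the remaining children are allocated.

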## Methods and analysis

2

### Study settings

2.1

This study aims to offer a thorough overview of digital rehabilitation research methodologies for ASD interventions, which will be achieved by comparing the intervention effects of a trial group (cognitive-behavioral training based on VR technology and early home intervention guided by a rehabilitation team) to those of a control group (early home intervention guided by a rehabilitation team). This study is planned as a randomized, controlled, parallel-group, non-inferiority trial with an equal allocation ratio between intervention and control groups. An overview of the protocol is illustrated in **Figure 1**.

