### Sample size calculation

2.2

The sample size was determined based on the primary outcome measure and the scores from the ADOS scale. Previous studies reported an average ADOS-2 score of 16.9 ± 4.1 for children with ASD (25). In this study, we hypothesized a clinically meaningful difference of 2 points in the intervention group compared to the control group, indicating the efficacy of the VR-based intervention. The required sample size was calculated using the PASS 15.0 software, with the stipulation of α=0.05 and the test efficacy 1-β=0.8. This process yielded a sample size of 72 patients. Given a 10% loss of visits, the calculated sample size for each group was 80, with a total sample size of 160 cases.

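### The trial is labelled non-inferiority with no margin, but its hypothesis, sample size and tests are those of a superiority trial, and non-inferiority of an add-on could not show that VR works

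*Protocol article*

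**What the plan says.** The label appears twice. The Introduction says: "This protocol describes an upcoming randomized, controlled, parallel-group, non-inferiority trial". Section 2.1 (Study settings) repeats it: "This study is planned as a randomized, controlled, parallel-group, non-inferiority trial with an equal allocation ratio between intervention and control groups". Neither place gives a margin, and no other section does.

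The rest of the article describes a different kind of trial:

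- **Aim** (Abstract, Discussion): "The primary aim of this trial is to determine the clinical effectiveness of cognitive training using VR technology in children with ASD".
- **Hypothesis** (Introduction): "We hypothesized that the intervention group would exhibit a potentially positive impact on ASD-related core symptoms", with the control group as comparator.
- **Sample size** (section 2.2): the calculation assumes "a clinically meaningful difference of 2 points in the intervention group compared to the control group, indicating the efficacy of the VR-based intervention".
- **Analysis** (section 3, Statistical analysis): independent-samples t-tests or nonparametric tests between groups, and repeated-measures ANOVA, with significance at p of 0.05 or less. No confidence limit is compared with a margin.
- **Arms** (Introduction, and again in sections 2.1 and 2.9): "The intervention group will receive cognitive behavioral training based on VR technology, in addition to early family intervention under the guidance of the rehabilitation team", whereas "the control group will receive only early family intervention under the guidance of the rehabilitation team". VR is therefore an add-on, not a replacement.

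**The concern.** A non-inferiority trial and a superiority trial test different null hypotheses. In the first, the null is that the new arm is worse by at least a stated margin. In the second, it is that the arms do not differ. The article names the first and builds the second, so the success criterion for the primary comparison is not settled.

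The add-on structure makes this more than a naming problem. Non-inferiority is informative when a new treatment replaces an established one. Here both arms keep the family intervention, so an added component that does nothing would be expected to meet a non-inferiority criterion. Such a result could not support the stated aim of showing that VR training is effective.

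With the label in place and no margin fixed, a null result could later be presented as successful non-inferiority against a margin chosen after the data are known.

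**Working it through.** **Inputs.** Section 2.2 gives SD 4.1 (mean 16.9), difference 2 points, α = 0.05 (sidedness not stated), power 0.80, 72 patients, 10% loss, 80 per group and 160 in total. The 72 must be per group, because 72 / 0.90 = 80 per group. Higher ADOS-2 scores mean more severe symptoms (section 2.7.5), so a positive difference (VR arm minus control) means the VR arm is worse.

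**1. The plan's own figure, read as superiority.** Two-sided 0.05, 80% power:

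n per arm = 2 × (1.960 + 0.842)² × 4.1² / 2² = 2 × 7.85 × 16.81 / 4 ≈ 66

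The exact t calculation gives 67. The stated 72 is not reproduced, but it errs on the conservative side. At 72 per arm the power is 82.8% (t) or 83.3% (normal). One-sided 0.05 with 90% power does give 72, but section 2.2 states 80%. This mismatch is minor and separate, and nothing below depends on it.

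**2. The same figures, read as non-inferiority.** With margin 2, true difference 0, one-sided 0.025 and 80% power, the formula is identical with the margin in place of the difference, and it again gives 66. The arithmetic therefore cannot tell the two designs apart. The wording of section 2.2 can: it presents the 2 points as a sought benefit, not as a tolerated loss.

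**3. What a non-inferiority rule would do here.** The article gives no margin, so one must be assumed. Two points is the only between-group difference it states.

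SE = 4.1 × √(2/72) = 0.683

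P(declare non-inferiority) = Φ((margin − true difference) / SE − z)

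| True VR effect on ADOS-2 | Margin (assumed) | One-sided α | Normal approximation | Exact t |
|---|---|---|---|---|
| none | 2 | 0.025 | Φ(2.927 − 1.960) = 83.3% | 82.8% |
| none | 2 | 0.05 | Φ(2.927 − 1.645) = 90.0% | 89.8% |
| 1 point worse | 2 | 0.025 | Φ(1.463 − 1.960) = 31.0% | 30.6% |
| 1 point worse | 2 | 0.05 | Φ(1.463 − 1.645) = 42.8% | 42.5% |
| none | 1 | 0.025 | Φ(1.463 − 1.960) = 31.0% | – |
| none | 3 | 0.025 | Φ(4.390 − 1.960) = 99.2% | – |

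**4. What a superiority rule would do.** A two-sided 0.05 test favours an inert VR programme in 2.5% of trials.

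**5. Sample size if non-inferiority were really meant.** With true difference 0, SD 4.1, one-sided 0.025 and 80% power, evaluable n per arm is 264 for a margin of 1, 118 for 1.5, 66 for 2, 30 for 3 and 17 for 4. Without a margin, the adequacy of 160 children cannot be judged.

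**The case against.** The strongest reply is that this is a mislabel in two descriptive sentences. Everything that governs inference points to superiority, and the only written decision rule is a difference test. If that test is two-sided, its false-positive rate in favour of VR is 2.5%. The 83–90% figures belong to a rule the article does not contain, and section 2.2 describes the 2 points as a benefit, not a margin. A non-inferiority label also does not exclude a superiority conclusion, since the same confidence interval can be checked against zero. Finally, the aims are mixed: section 2.1 gives the primary objective as creating and applying the training system, and section 4.2 speaks of feasibility and safety.

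Part of this stands. The large probabilities are conditional on an assumed margin and do not describe the written test. Superiority is needed for the efficacy aim, not necessarily for the others. The repair is mainly one of wording.

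It does not remove the finding. The design is labelled this way twice, once in the section that defines it. Checking the interval against zero after non-inferiority is legitimate when both hypotheses and their order are stated in advance, and here neither is. Nor is this detail that an article leaves to a fuller document: the article itself fixes a label together with a hypothesis, a sample-size basis and a test rule that do not fit it.

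**Conclusion.** The concern holds. The article contradicts itself on the null hypothesis and success criterion of its primary comparison, and the non-inferiority reading cannot answer the efficacy question for an add-on treatment. Under that reading the chance of a success claim for an inert VR programme is set almost entirely by the margin: 31% at 1 point, 83% at 2 and 99% at 3, against 2.5% under a two-sided superiority test. These figures assume 72 evaluable children per arm, SD 4.1 in both arms, one-sided 0.025 and margins that are ours, not the article's. The contradiction itself does not depend on any of these assumptions. It must be corrected before the results are known.

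**What to change.** 1. Replace non-inferiority with superiority in the Introduction and in section 2.1.
2. State the null hypothesis: no difference in ADOS-2 score between VR plus family intervention and family intervention alone, tested at two-sided α = 0.05. The article does not state sidedness, so it should be added to section 2.2. The statement should also say which of the six assessments in section 2.1 is the primary time point.
3. State the success rule: efficacy is concluded only if the 95% confidence interval for the between-group difference excludes zero in favour of VR.
4. Date the amendment and record that it was made before any comparative data were seen, because section 2.4 reports recruitment since 24 December 2024. Check whether the registry entry carries the same label and align it if so.

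**Cost.** This is a wording amendment, with no change to recruitment or procedures. Superiority needs 67 evaluable per arm, or 67 / 0.90 = 74.4, rounded up to 75 after 10% loss. The planned 80 cover this.

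If the investigators do intend non-inferiority, the article instead needs a justified margin, a confidence-limit rule, a sample size recalculated from that margin, and an explanation of what non-inferiority of an add-on would establish.
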